## 7.2 Stream 2 Participant Identification

The BCSP has a process whereby any patient who is identified as requiring further bowel investigation (either from a flexible sigmoidoscopy or a positive FOBt) is invited for an initial colonoscopy as part of the BCSP as described in Section 5.2.1.

As part of routine care, the BCSP team post a NHS health questionnaire to their patients who are on the 1 and 3 year CSP waiting list 10 weeks in advance of their colonoscopy appointment and request that this is posted back to BCSP team. Within this envelope will be a Study Introduction Letter (Annex 3) which briefly introduces the MOTION study and explains that the MOTION Study PIL, Summary PIS and Full PIS will be posted to them within a few days. There will also be a free post envelope for the participant to send the Stream 2 reply sheet (Annex 8.2).

The CSP Health Questionnaire and the MOTION Study information will be sent separately in case of confusion with return envelopes. The MOTION study envelope will have a MOTION Study sticker placed on the back of the envelope so that this prompts the participant to place the study reply sheet in to this envelope.

The Study Researcher will inform the CSP team which of their patients have responded to the study and subsequently given written informed consent for the study. This is so that the CSP team can inform the Study Researcher of when the next routine care colonoscopy will be due as part of the routine CSP (the participant will have consented to this sharing of information between the Study Researcher and the CSP). For non-responders to the study, the CSP team will not contact their patients again for study purposes.

At the point of consenting, it will not be known if any participant from stream 2 has any inflammatory bowel condition (Ulcerative Colitis, Crohn's Disease or Diverticulitis). Following the routine care colonoscopy, if a participant is found to have any of these conditions, they will not be withdrawn from the study.

Stream 2 will potentially identify participants for cohorts 1, 2 & 3 (Figure 3).

The current number of patients (as at January 2019) on the waiting list for a scheduled colonoscopy as part of the CSP are as follows: -

01/01/2019 – 31/12/2019

494 patients due for 1 or 3 year surveillance (1 year surveillance patients, only until June 2019).

01/01/2020 – 31/12/2020

531 patients due for 3 year surveillance.

01/01/2021 – 31/12/2021

340 patients due for 3 year surveillance (3 year surveillance patients, only until June 2021).

[figure not shown]

### 7.3 Stream 3 Participant Identification.

Approximately 200 GP referrals per week are received by the Memory Assessment Services in Norwich, South Norwich, North Norwich/Norfolk, Great Yarmouth and Lowestoft. When referred patients are seen for a memory assessment by the Community Teams for each area, they are asked to sign a Consent to Research form (Annex 12). The NSFT Research Team can then approach those participants with a diagnosis of MCI that have completed this form. This team comprises of

experienced research nurses who are led by [name] (Senior Research Nurse).

Through engagement with the NSFT Clinical Teams, MCI participants will be identified in clinics and approached by the Clinical Teams and provided with a brief introduction to the study. They will also be offered the study flier (Annex 6.1). The participant can then request for the study information (PIL, Summary PIS and Full PIS to be sent to them. The participant can then return the Stream 3 reply sheet (Annex 8.3) via the free post envelope directly to the NSFT Research Team.

Collaboration with the NSFT Clinical and Research teams will therefore enable identification of suitable participants who have a diagnosis of MCI and be suitable for cohort 3 and in some instances, potentially cohorts 1 and 2. NSFT links with JDR will also enable identification of suitable participants. All consented participants will undergo the same cognitive testing as part of the screening and final eligibility process in the Pre-Study Visit.

Streams 1 & 2 will not be aware that Stream 3 participants will be seen in their home for the Pre-Study Visit and vice versa.

The overall collaborative recruitment strategy is shown in Figure 4.

[figure not shown]

MOTION Study Recruitment Strategy.  
Figure 4.

To summarise:

- Streams 1 & 2 will have 10 visits at QI CRF and Stream 3 will have 9 visits at QI CRF (see Section 7.3).
- There are two subgroups in this study (Sections 5.2.1 and 5.2.2).
- All participants will be required to attend Beccles Hospital for OCT/OCT (A) scans (Section 9.1.2) and 30 participants from cohort 3 will undergo brain MRI scans at the NNUH (Section 5.2.2).

#### 7.4 Inclusion Criteria

- + Male or female aged at least 60 years.
- + Must be able to understand the study and provide signed and dated informed consent.
- + Must be able to complete the Cognitive Tests/Questionnaires, Health Questionnaires by themselves and be familiar with using an ipad/tablet. The device will be provided by the Study Researcher and any support required will be available.
- + Participants who have MCI would be eligible to participate providing they satisfy all other criteria.
- + Over a period of 4 years, participants must be willing and able to attend the QI CRF 10 times. Participants with MCI will be seen in their own home once by a member of the NSFT Research Nurse team for the Pre-Study Visit and will then need to attend the QI CRF 9 times for the remaining study visits.

Participants must be willing and able to do the following at QI CRF: -

- + Produce stool samples at home which they will bring to to QI CRF within 24 hours of production.
- + Provide blood samples (255 ml in total = 51 teaspoons). There is no requirement to fast for blood sampling.
- + Complete health and lifestyle questionnaires (some may be posted from home).
- + Undergo height, Tanita Scales Measurement, BP and hand grip strength measurements.
- + Undergo cognitive assessment tests.
- + All participants will need to attend Beccles Hospital for Optical Coherence Tomography OCT scans. Those participants in subgroup 1 will receive an OCT (A) scan around the Baseline Visit and Study Visit 8.

✚ 30 participants in subgroup 2 will be requested to undergo a brain MRI at NNUH 4-6 weeks from the Baseline Visit and 4-6 weeks prior to Study Visit 8. This is optional.

It will be explained to all participants that they will be fully supported by the NSFT Research Nurse/Study Research Team for all the procedures, tests and questionnaires that the participant will be required to undertake at each Study Visit. It is acknowledged that the study is complex by nature, therefore where possible, all participants will be encouraged to bring their partner/relative/friend to all the Study Visits to reduce any anxiety.

## 7.5 Exclusion Criteria

The participant may not enter the study if ANY of the following apply:

- ✚ Currently taking part in an interventional study.
- ✚ Living with or related to any member of the research team.
- ✚ Have a diagnosis of Dementia, Parkinson's Disease, Alzheimer's Disease, Creutzfeldt-Jakob disease (CJD), Picks Disease. **Mild Cognitive Impairment is not an exclusion.**
- ✚ Schizophrenia
- ✚ Bipolar Disorder
- ✚ Obsessive Compulsive Disorder
- ✚ Untreated current clinical depression
- ✚ Have irreversible brain injury.
- ✚ Have had a stroke.
- ✚ Have epilepsy.

Any participant who develops any condition listed above in the exclusion criteria following informed consent will be withdrawn from the study. See Section 5.

Any participant who develops any condition listed below in the exclusion criteria following informed consent will not be withdrawn from the study. However, individual cases may be assessed by the study team.

- ✚ Take more than a daily dose of probiotics.
- ✚ Have a long-standing gastrointestinal or liver function abnormality requiring on-going medical management or medication.
- ✚ History of cancer within the last 5 years except for squamous or basal cell carcinomas of the skin that have been medically managed by local excision.

- ✚ Unstable dietary history as defined by major changes in diet during the previous month, where a major food group in the diet has been stopped or significantly increased, for example become vegetarian, vegan or stopped eating red meat.
- ✚ History of alcohol, drug or substance abuse.
- ✚ History of Hepatitis B or Hepatitis C.
- ✚ Major surgery of the gastrointestinal tract, apart from gall bladder or appendix removal, in the past five years.
- ✚ Any major bowel resection at any time.
- ✚ History of Ulcerative Colitis, Crohn's Disease or Diverticulitis.
- ✚ Persistent, infectious gastroenteritis, colitis or gastritis, persistent or chronic diarrhoea of unknown cause, *Clostridium difficile* infection (recurrent) or *Helicobacter pylori* infection (untreated).
- ✚ Constipation.
- ✚ Regular use of laxatives.

The Full PIS requests that the participant informs the Study Researcher of any change in their medical history. As a secondary measure, the GP Information Letter also requests this information.

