Age is a major risk factor for the development of cognitive dysfunction with dementia being one of the most common disorders linked to ageing [7]. Dementia affects an estimated 47 million people worldwide and is projected to affect over 131 million people by 2050 [8]. Cognitive function declines with age, ranging from relatively minor everyday slips of action, through subjective cognitive decline, mild cognitive impairment (MCI), then to major or mild neurocognitive disorder/dementia in some instances. Up to 50% of those with MCI are predicted to develop dementia within 5 years [9].

The development of new treatments to prevent dementia is hindered by a lack of predictive biomarkers. The gut microbiome is a potential marker for progressive declining intrinsic capacity, which is a composite of all the physical and mental attributes on which an individual can draw, not only in older age but across their lives. Evidence of age-associated changes in the gut microbiome comes from population-based studies, one of the largest and most comprehensive was ELDERMET, a study that examined the faecal microbiome of elderly individuals living in the community or in care homes in Ireland [10]. The results identified differences in the composition of the gut microbiome of elderly individuals compared with younger individuals, and that these differences were associated with poorer health status in the elderly (e.g. poor dentition, dysphagia, loss of salivation, decreased physical activity and constipation).

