Participants in cohort three will be populated with individuals with mild cognitive impairment (MCI) which refers to cognitive decline from a previous level of functioning. Both subjective and objective evidence are used to identify currently healthy ageing individuals who are at a high risk of developing dementia longitudinally [20]. Data from eleven studies carried out across six countries have suggested that MCI is a surprisingly common condition, especially in industrialized nations, affecting between 5 and 37% of the studied populations [21]. It is important to note however that MCI is not the same as a diagnosis of dementia because up to 40% of MCI patients revert back to health within 12 months [22]. We are confident that high, medium and low risk participants can be identified over the participant recruitment period of 2 years, even with a possibly higher dropout rate for the high and medium-risk subjects.

We expect to identify in excess of 3,500 potential participants with MCI (Norfolk and Clinical Commissioning Group prevalence figures provided by [name], Head Public Health Information, Norfolk County Council, April 2018) using objective cognitive deficits; from an annual conversion rate of 10% to dementia, this will make it possible to identify at least 120 high-risk participants within the recruitment period. This assumes that 50% of those meeting the eligibility requirements can potentially be recruited to the study. In assuming an annual attrition rate of ~20%, our conservative estimate is that the number of participants required can be recruited within 2 years.

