## 16 EARLY TERMINATION/DISCONTINUATION/WITHDRAWAL OF PARTICIPANTS FROM STUDY

Each participant has the right to withdraw from the study at any time. In addition, the Investigator may discontinue a participant from the study at any time if the Investigator considers it necessary for any reason including:

- ❖ Cognitive test result at the Pre-Study Visit does not fall within the required threshold (Annex 26). This will also apply in the event of any cohort that already has the maximum number of 120 participants.
- ❖ Withdrawal of Consent (Annex 28).
- ❖ Ineligibility (either arising during the study or retrospectively having been overlooked at screening). See Section 7.5.
- ❖ Significant protocol deviation.
- ❖ Significant non-compliance with study requirements.
- ❖ Lost to follow up.

The reason for withdrawal will be recorded in the Study Withdrawal Log and the participant and their GP will be sent a Withdrawal Letter (Annex 27) from QIB explaining the reason for withdrawal. Participants who send their Study Withdrawal Postcard (Annex 29) will be sent a Participant Self-Withdrawal letter (Annex 28). Annexes 28 and 30 will explicitly state that the participant should contact the QIB Researchers if they wish to have any samples or data already collected to be destroyed, otherwise these will be included in the analysis.

Withdrawn participants or participants who withdraw themselves will not be replaced. In the event of Early Termination or Withdrawal, there will not be any additional visits.

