### **Longitudinal analyses (after successive waves and following completion of all data collection)**

Detailed analyses plans will be prepared following data collection but ahead of any analysis after each visit, building on the cross-sectional findings, but in brief planned analyses will address the following questions:

6. What is the intra-individual variation and trajectory of different components of the gut microbiome with age?
7. How does the baseline composition of the gut microbiome predict future changes in clinical outcomes? Eg, among people with mild cognitive impairment, can analysis of the gut microbiome be used to predict future cognitive change.
8. How do changes in the gut microbiome correlate with changes in clinical outcomes?

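### Mandatory withdrawal on a dementia, Alzheimer's or Parkinson's diagnosis would end observation in about a third of Cohort 3 and can bias the cognitive-change analyses in that cohort

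*Protocol*

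**What the plan says.** Section 7.5 splits the exclusion criteria into two lists. For the upper list, "Any participant who develops any condition listed above in the exclusion criteria following informed consent will be withdrawn from the study". That list contains "Have a diagnosis of Dementia, Parkinson's Disease, Alzheimer's Disease, Creutzfeldt-Jakob disease (CJD), Picks Disease", together with several psychiatric conditions, brain injury, stroke and epilepsy. Participants who develop a lower-list condition are kept.

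Section 16 adds: "In the event of Early Termination or Withdrawal, there will not be any additional visits", and "Withdrawn participants or participants who withdraw themselves will not be replaced". Samples and data already collected are kept unless the participant asks for their destruction: "otherwise these will be included in the analysis". Section 16 words discontinuation by the investigator as permissive, whereas Section 7.5 is mandatory. Section 23.7.1 separately withdraws participants who are losing capacity.

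Section 5.1 defines the cohorts by risk of dementia, with 120 in each, and Cohort 3 is the high-risk group. One of the longitudinal questions in Section 19.1 is whether, "among people with mild cognitive impairment, can analysis of the gut microbiome be used to predict future cognitive change". Section 19.2 calls the link between the microbiome and longitudinal clinical change a primary aim and bases power on cognition.

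**The concern.** The rule makes the outcome of interest a reason to stop observing it. A participant in Cohort 3 who declines far enough to be diagnosed leaves the study even if willing and able to continue, because loss of capacity has its own rule in Section 23.7.1.

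Section 7.5 points to Section 5 for the reason. That text concerns conditions present at baseline and argues that a condition acting on cognition by an alternative process adds noise. Incident dementia in a cohort selected for dementia risk is not present at baseline, and it is not an alternative process.

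At stake are the Cohort 3 analyses. If decline leads to withdrawal before it is recorded, average decline in the cohort looks too small. A microbial feature that speeds decline also loses more of its carriers, which pulls its estimated effect toward zero. An analysis plan can choose a better model, but it cannot recover scores, stool samples or scans that were never collected.

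**Working it through.** **Expected withdrawals in Cohort 3 (n = 120)**

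Inputs: the Section 5.1 recruitment estimate, which works "from an annual conversion rate of 10% to dementia"; the Section 1.1 upper figure, "Up to 50% of those with MCI are predicted to develop dementia within 5 years"; and the Section 5.1 statement that up to 40% of MCI patients revert within 12 months.

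- 10% a year for 4 years: 1 - 0.9^4 = 0.344; 0.344 × 120 = 41.
- 10% a year to the last cognitive test at 42 months (Study Visit 7): 1 - 0.9^3.5 = 0.308; 0.308 × 120 = 37.
- Upper: 50% in 5 years gives 1 - 0.5^(4/5) = 0.426; 0.426 × 120 = 51.
- Lower: if 40% revert and never convert, 0.6 × 0.344 = 0.206; 0.206 × 120 = 25.

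A 20% loss from 360 is 72 people. The central figure of 41 equals 57% of that allowance (41/72), yet Section 19.2 attributes the allowance to death and dropout only. In the MRI subgroup of 30 from Cohort 3, 0.344 × 30 is about 10 who would convert over the period and could miss the closing scan.

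**Power**

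The plan's own figure was reproduced first. Treating four-year change as a two-group comparison with SD 2.2, two-sided alpha 0.05 (sidedness assumed) and N = 300 split 75/225:

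- SE = 2.2 × √(1/75 + 1/225) = 0.293; 0.8/0.293 = 2.73; power = Φ(2.73 - 1.96) = 78%, against 77% in the Section 19.2 table for 0.8 points at 25% prevalence.

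Suppose all 41 come on top of the planned losses. N is then 300 - 41 = 259, or 288 - 41 = 247 if 20% of 360 is taken literally. Power becomes about 72% or 70%. This is a worst case, since some of the 41 may already be in the allowance and their earlier scores are retained.

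**Bias (illustrative simulation)**

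Setting: 360 participants, one third in Cohort 3; tests at 0, 6, 18, 30 and 42 months; random-intercept-and-slope mixed model; withdrawal calibrated to 10% a year in Cohort 3. The true feature effect is -1.00 point over 4 years at 25% prevalence, and the true extra decline in Cohort 3 is -1.20. Score levels, slopes, error and the link from score to diagnosis are assumptions; the protocol does not give them. The two middle columns are two variants of withdrawal driven by cognition not yet recorded.

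| Quantity | Full follow-up | Underlying level | Current score | Last recorded score |
|---|---|---|---|---|
| Effect, all 360 | -1.03 | -0.99 | -0.97 | -1.03 |
| Effect, Cohort 3 only | -1.00 | -0.88 | -0.83 | -1.01 |
| Extra Cohort 3 decline | -1.21 | -0.94 | -0.79 | -1.22 |

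- Cohort 3 effect: 12% to 17% too small under unrecorded decline.
- Extra Cohort 3 decline: 22% to 34% too small. With a smaller error setting (0.6 instead of 1.0) it was -1.02, or 15% too small.
- All 360: 4% to 6% smaller than under full follow-up.
- Last recorded score: essentially no bias in any row.

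A second simulation treated everyone as Cohort 3-like (34% withdrawn, effect 0.8 points over 4 years, mean decline 0.5 points a year). It attenuated the feature effect by 16-23%. A further run with the 0.8-point effect, 25% prevalence and one third in Cohort 3, with limited replication, gave about 6% for the pooled sample, against 23% when everyone was treated as Cohort 3.

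**The case against.** Several counter-arguments carry weight.

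- **Mechanism.** Under Section 10.1 the GP receives copies of the cognitive tests, so a diagnosis may follow recorded scores, at least in part. Scores before withdrawal are kept. If withdrawal depended only on recorded scores, a mixed model would show no material bias. This stands as the lower bound. However, cognition is tested only every 12 months after month 6, and the diagnosis comes from outside the study, so some unrecorded decline is realistic.
- **Scope.** A reader might infer that the whole study's cognitive analysis is attenuated by about a fifth. The documents do not support that. The power analysis in Section 19.2 concerns the full sample, where the simulated bias is small; the larger figures belong to Cohort 3 alone.
- **Conversion as an outcome.** A reader might also infer that conversion to dementia is lost altogether. It is not. The Withdrawal Log holds the reason for withdrawal, and consent covers access to GP and hospital notes (Sections 16 and 11.1). What is lost is later scores, samples and scans.
- **Rationale.** Section 5 also names effects on the microbiome and a wish to describe normal variation, and Section 1.1 reports altered microbiota in Parkinson's and Alzheimer's disease. That is some reason for care, but it is worded for baseline. For stroke or epilepsy the alternative-process argument can apply, so those conditions are outside this point.
- **Rates.** Cohort 3 is defined by Mini-ACE and CCI cut-offs, so 10% a year may not transfer. Section 5.1 does foresee possibly higher dropout in the medium- and high-risk groups, but Section 19.2 does not carry this into its allowance.
- **Priority.** The stated primary objective is descriptive, and Section 23.7.1 would still remove some affected participants. Both points limit the severity.

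**Conclusion.** The point holds for incident dementia, Alzheimer's disease and Parkinson's disease. The protocol stops observing participants when they reach the end of the pathway that Cohort 3 and the MCI question are meant to study, and its stated rationale does not justify this. The withdrawal count follows from the protocol's own rate, provided that rate applies to Cohort 3 as defined. The size of the bias does not follow from the protocol: it depends on assumed slopes, error and, above all, on how far withdrawal runs ahead of recorded scores. Under the unfavourable mechanism it is material within Cohort 3; in the full sample it is minor, and under the favourable mechanism it is negligible.

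This should be fixed, because data not collected cannot be recovered later. It does not threaten the descriptive primary objective, and the harm lies mainly in the Cohort 3 cognitive-change analyses.

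**What to change.** - In Section 7.5, remove incident dementia and related neurodegenerative diagnoses from the mandatory-withdrawal list. Continue the study assessments already scheduled while the participant has capacity and consents. The capacity rule in Section 23.7.1 stays.
- For those who stop visits, record the date and type of diagnosis from GP and hospital notes, and state in the consent material that this continues after visits end.
- In Section 19.2, state the expected number of withdrawals for dementia within the loss allowance.
- Reconcile the mandatory wording of Section 7.5 with the permissive wording of Section 16.

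The choice of model for informative dropout can be left to the analysis plans promised in Section 19.1.

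Cost: one amendment to the protocol and information sheet, and no visits beyond those already planned. Later assessments will be harder for affected participants and less complete, so full follow-up is an upper limit on what the change can achieve.
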